#### Planned statistical analysis

Analysis in the current study will employ regression models controlling for the hierarchical structure of the data to compare the active intervention versus controls adjusting for baseline level. Presentation of the data will be in accordance with Consort guidelines [17]. Several models will be run to test for the main treatment outcomes, implementation outcomes, and related research questions. Missing data will be estimated in the models using full information maximum likelihood estimation, a well-established technique that allows for the inclusion of all available data and estimation of missing values [29].

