### Randomization

Participants are randomized at the school-level. Because schools are randomized only once when they join the study, study participants may know prior to offering their consent for participation whether they would receive EMOTION or be in a control school being offered treatment as usual (TAU). The schools will be matched prior to randomization based on geographic location (municipality) and school size. Randomization is to be conducted by coin flip and the results corroborated by an external expert cooperating with a member of the research support team at RBUP. Thirty-six schools are included to have a balanced design with an equal number of schools in each design arm and to ensure that the sample of students in the experimental condition is large enough to detect the expected effect size for the main outcome. Group sizes were limited to maximum seven students per group so that group leaders had a reasonable group size to manage. When the number of students who meet inclusion criteria exceeds the group maximum size, a group of seven students is randomly selected to fill the group.

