### Data analysis

The study is carried out in schools and therefore data analyses will be conducted in a multilevel modeling framework to account for non-independence of the participants at the school level.

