#### Sample size

The power estimation was based on an equation recommended accounting for a multi-level approach [25]. A total of 559 children (see Table 2) were deemed necessary to test the effectiveness of the intervention given the desired significance level (0.05), required power (0.80), and the following conditions:

**Table 2 Tab2:** Number of participants and clusters required in a multilevel study

Estimated ICC	Calculated DEFF	Number of children	Number of schools
0.00 - Base model	1	260	15
0.05 - Two-level model	2.15	559	23(36)^a^

*ICC* the intraclass correlation coefficient, *n* number of pupils, *DEFF* design effect = 1 + (nc - l)*ICC, (*nc* average number of individuals in a school = 24); The first value (260) is from Altman [26], page 456, and the next figures are multiplied with the calculated DEFF value

^a^The first number denotes the required sample size given the power calculation. The parenthetical number denotes the actual number of schools recruited for the study based on other practical considerations

anticipated effect size in anxiety and depression are 0.35, a conservative estimate based on previous studies [27],the expected intraclass correlation coefficient (ICC estimate .05) based on previous research showing low ICCs within Norwegian schools [28],average size of the clusters = 24 (i.e.: number of individuals expected in the EMOTION group within each school in a two-year period).

Because the school sizes were small for some of the more rural areas, it would be impossible to recruit large enough cohorts every semester to run an EMOTION group (minimum of three participants per group). The decision was made to recruit more schools to the study (cluster *N* = 36) to increase the participation in the intervention group. A further consideration driving this decision was that EMOTION groups are limited to a maximum of seven students per group in order to allow for adequate group facilitation by the group leaders. This decision had the knock-on effect of increasing the number of clusters and decreasing within-cluster dependence, which improves the power for detecting smaller effect sizes.

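### Schools are matched on municipality and size before randomization, but the stated model does not name these factors, so the reported standard errors may be conservative

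*Protocol article*

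**What the plan says.** The Randomization section restricts the allocation: "The schools will be matched prior to randomization based on geographic location (municipality) and school size". It continues "Randomization is to be conducted by coin flip", and fixes 36 schools with equal numbers in the two arms. It does not say whether the matched sets are pairs or larger.

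The Data analysis section gives the purpose of the multilevel framework as "to account for non-independence of the participants at the school level". Planned statistical analysis then describes "regression models controlling for the hierarchical structure of the data to compare the active intervention versus controls adjusting for baseline level" and adds that several models will be run. Neither section mentions municipality, school size or the matched set. Neither excludes them.

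The Sample size section uses a design effect alone and takes no credit for matching.

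**The concern.** When allocation is restricted by matching, schools in a matched set share whatever municipality and size contribute to the outcome. That shared part cancels from the difference between arms. A model with only a school random effect and a baseline covariate treats the schools as allocated without restriction, so it leaves the shared part in the between-school variance that feeds the standard error.

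The stated standard error is then larger than the true sampling variability, intervals cover more than 95%, and the test rejects less often than 5% under the null. The information about the treatment effect comes from only 36 schools, so precision earned in the design should show in the analysis.

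**Working it through.** **Plan's own figures.** Two-sided 5% significance, 80% power and an effect of 0.35 SD give 129 children per arm, 258 in total, against the stated 260. (The article does not state sidedness; two-sided reproduces its figure.) The design effect is 1 + (24 − 1) × 0.05 = 2.15, and 260 × 2.15 = 559. Then 559 / 24 = 23.3, the stated 23 schools. These figures reproduce.

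**Inputs.**
- From Sample size and Randomization: ICC 0.05, effect 0.35 SD, 559 children, 36 schools, hence 18 per arm and 559 / 36 = 15.5 children per school. The article's own planning value is "average size of the clusters = 24"; it is used below as a sensitivity check.
- Assumed: *f*, the share of between-school variance that municipality and size explain beyond baseline. The article gives no value, so a range is shown.
- Total variance is set to 1, with no reduction credited to the baseline covariate.

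**Formulas.**
- Variance of a school mean, matching ignored: V0 = 0.05 + 0.95 / 15.5 = 0.111.
- Variance of a school mean that is left in the arm contrast: V1 = 0.05 × (1 − *f*) + 0.95 / 15.5.
- Standard error of the difference: √(2V / 18).
- Excess width: √(V0 / V1). True type I error: 2 × [1 − Φ(1.96 × √(V0 / V1))].
- Power loss: power at 0.35 SD using the correct standard error, minus power using the V0 standard error when the true standard error is based on V1.

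| *f* (assumed) | V1 | SE reported | SE true | Ratio | True type I error | Power loss |
|---|---|---|---|---|---|---|
| 0 | 0.111 | 0.111 | 0.111 | 1.00 | 5.0% | 0 |
| 0.25 | 0.099 | 0.111 | 0.105 | 1.06 | 3.7% | 2.0 points |
| 0.50 | 0.086 | 0.111 | 0.098 | 1.14 | 2.6% | 3.5 points |
| 0.75 | 0.074 | 0.111 | 0.090 | 1.23 | 1.6% | 4.4 points |

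With 24 children per school the ratios at 0.25, 0.50 and 0.75 are 1.08, 1.18 and 1.31.

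**Simulation check** (matched pairs, *t* reference with 34 df, matching ignored, ICC 0.05). Coverage of the nominal 95% interval was 95.0, 96.2 and 97.2% at *f* = 0, 0.25 and 0.50, and 99.0% at *f* = 1. Power at 0.35 SD ran from 0.865 at *f* = 0 to 0.924 at *f* = 1.

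**Cost of adjusting.** Ignoring matching leaves 36 − 2 = 34 school-level df. Suppose adjustment spends three of them (for example two for region and one for size), leaving 31. At *f* = 0 the interval ignoring matching is 0.996 times the adjusted one, so adjustment costs about 0.4% in width. At *f* = 0.25 and 0.50 the ratio is 1.06 and 1.13 in favour of adjustment.

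A strict pair analysis has only 17 df. It gives the narrower interval only if *f* exceeds about 0.16 (0.13 with 24 children per school).

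**The case against.** The strongest objection is that this is a condensed article. It names baseline level as an adjustment but does not call it the only one, and a fuller covariate list may sit in an analysis plan that is not shown. A reader might infer that the plan excludes the matching factors; the text does not support that. What remains is that the article does state a model, and the factors that restrict its own randomization are not part of that statement.

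A reader might also infer that the precision bought by matching is lost. It is not. Matching balances the arms whatever model is fitted: the true standard error falls from 0.111 to 0.105 and 0.098 at *f* = 0.25 and 0.50. Only the reported standard error misses the gain.

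Nor is it certain that intervals are too wide. That depends on a prognostic strength the article does not give. Baseline adjustment may absorb part of it, and at *f* = 0 nothing is missed. Against a pair analysis, ignoring matching even gives the narrower interval below the break-even share. That threshold does not apply to covariate adjustment, which costs almost nothing when the factors are uninformative.

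Finally, the error is in the safe direction, and the sample size never relied on matching. Both points stand, and they keep the severity low.

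**Conclusion.** The point holds as a conditional matter of efficiency. To the extent that municipality and school size predict outcome beyond baseline, the model as stated will report standard errors that are too large and a test that is conservative. At ICC 0.05 with 36 schools of 15.5 children, intervals would be about 0, 6, 14 or 23% too wide for assumed shares of 0, 25, 50 or 75%, with a power loss of about 0 to 4 points.

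The documents do not support reading this as a threat to validity or to the planned power. Type I error is at or below 5% throughout, and simulated power with matching ignored stays above 0.80 at the planned ICC. That last statement rests on ICC 0.05. If the ICC were 0.10 and baseline explained nothing, simulated power with matching ignored would be 0.745 and 0.766 at shares of 25 and 50%, against 0.775 and 0.855 for a pair analysis. Most of the shortfall from 0.80 at the smaller share comes from the higher ICC, not from how matching is handled. If baseline explained 36% of the variance, the figures with matching ignored would be 0.912 and 0.931.

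Severity is low.

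**What to change.** State in the planned analysis that every primary model includes the matching factors as covariates: municipality (or region where municipalities hold few schools) and school size. Alternatively, include the matched set as a random effect. Fix the choice before outcome data are examined, so that it cannot depend on the results.

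Both factors are already used to match the schools, so no new data are needed. The cost is one sentence and a few school-level degrees of freedom. The exact number depends on how many municipalities take part, which the article does not give for the central and southeastern sites; using region keeps it small.

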#### Inclusion criteria

The children who agree to take part in the study fill out the Short Mood and Feeling Questionnaire for depression (SMFQ) [14, 15] and Multidimensional Anxiety Scale for Children (MASC) [16]. All of the children who fill out the screening questionnaires who score at least one standard deviation above the expected mean score for either depression (SMFQ; *M* = 3.8, *SD* 3.6), anxiety (MASC; girls *M* = 46, *SD* 15; boys *M* = 39, *SD* 15), or both, are then invited to join the study.

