#### Primary outcomes

The primary outcomes of interest for this study are the changes in depression and anxiety from pre- to post-intervention and from pre-intervention to follow-up. The null hypotheses for the primary outcomes of this study is that there will be no significant differences in changes of depression or anxiety scores between the intervention and the control groups. Depression is assessed using the SMFQ [14], a 13-item measure assessing cognitive, affective, and behavioral-related symptoms of depression in children 8 to 18 years. Anxiety is assessed using the MASC [16], a 39-items self-report measure for adolescents between 8 and 19 years.

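### Sex predicts MASC by the protocol's own norms but is not named in the outcome model; adding it would be a small, free improvement for the MASC analysis

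*Protocol article*

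**What the plan says.** All references are to the protocol article.

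- **Inclusion criteria.** Children enter if they "score at least one standard deviation above the expected mean score for either depression", for anxiety, or for both. The MASC norms differ by sex ("girls *M* = 46, *SD* 15; boys *M* = 39, *SD* 15"). The SMFQ has one norm for all children ("SMFQ; *M* = 3.8, *SD* 3.6").
- **Primary outcomes.** The null hypothesis is "no significant differences in changes of depression or anxiety scores between the intervention and the control groups". The target is a contrast between arms.
- **Planned statistical analysis.** Regression models that respect the clustering are to be used "to compare the active intervention versus controls adjusting for baseline level". Baseline level is the only adjustment stated. The section does not say that it is the only one allowed, and it adds: "Several models will be run to test for the main treatment outcomes, implementation outcomes, and related research questions".
- **Randomization.** "The schools will be matched prior to randomization based on geographic location (municipality) and school size". Sex is not a balancing factor. The same section says that families may know their school's arm before they consent, and Blinding says that most know it before the baseline assessment.

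**The concern.** When two groups have different long-run means, members with the same score today are expected to have different scores later, because each group regresses towards its own mean. On the protocol's norms, a girl and a boy with equal baseline MASC are expected to differ at T3 and T4 even without any intervention. A single regression line on raw baseline score cannot represent that.

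This has two possible consequences for the arm contrast. First, if the share of girls differs between arms, part of the sex difference passes into the estimated MASC effect. Such a difference is possible here: allocation is by school, sex is not balanced by design, and children come forward by open invitation, often knowing their arm. Second, even with a perfect balance, the unexplained sex difference stays in the residual and costs a little precision.

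**Working it through.** **The plan's own figure.** With effect size 0.35, two-sided alpha 0.05 and power 0.80, the standard two-mean formula gives 129 per arm, or 258 in total; the article uses 260. The design effect is 1 + (24 − 1) × 0.05 = 2.15, and 260 × 2.15 = 559, as stated. The sample size reproduces and is not at issue.

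**Inputs from the article.** MASC mean 46 (girls) and 39 (boys), SD 15, so the gap is 7 points, or 7/15 = 0.47 SD. The MASC entry points are 46 + 15 = 61 and 39 + 15 = 54. The planned effect is 0.35 × 15 = 5.25 MASC points, on the norm SD.

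**Assumed, because the article does not give them.** Baseline-to-outcome slope *b* from 0.4 to 0.8; the seven-point norm gap holds among enrolled children and persists over time; equal numbers of girls and boys for the variance calculation; a difference *d* in the share of girls between arms.

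**Formulas.**

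- Expected later score: E[Y | x, sex] = mean(sex) + *b* × (x − mean(sex)). At equal baseline x, the girl-minus-boy gap is 7 × (1 − *b*).
- Shift in the treatment effect when sex is left out: about *d* × 7 × (1 − *b*).
- Extra residual variance with half girls: gap² × 0.25 / [225 × (1 − *b*²)].

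| Slope *b* | Gap at equal baseline | Shift, *d* = 10 points | Shift, *d* = 20 points | Extra residual variance |
|---|---|---|---|---|
| 0.4 | 4.2 | 0.42 (0.028 SD) | 0.84 (0.056 SD) | 2.3% |
| 0.5 | 3.5 | 0.35 (0.023 SD) | 0.70 (0.047 SD) | 1.8% |
| 0.6 | 2.8 | 0.28 (0.019 SD) | 0.56 (0.037 SD) | 1.4% |
| 0.7 | 2.1 | 0.21 (0.014 SD) | 0.42 (0.028 SD) | 1.0% |
| 0.8 | 1.4 | 0.14 (0.009 SD) | 0.28 (0.019 SD) | 0.6% |

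Against 5.25 points, the shift is 0.14/5.25 = 3% to 0.42/5.25 = 8% at a 10-point imbalance, and 0.28/5.25 = 5% to 0.84/5.25 = 16% at 20 points. With *d* = 0 it is zero. More girls in the EMOTION arm would make the benefit look smaller; more girls in the control arm would make it look larger.

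**Check by simulation under the stated entry rule.** Children were selected on either scale, and SMFQ was assumed to add nothing about later MASC once baseline MASC is known. The true effect was −5.25. With *b* = 0.5 and 55% against 45% girls, the baseline-only model gave −4.93 and the model with sex gave −5.25. With *b* = 0.7, the two gave −5.03 and −5.22. The shifts are close to the formula, and slightly smaller because baseline score carries a little of the sex difference.

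**Check of the whole trial.** This used 36 schools of 16 children (559/36 = 15.5), ICC 0.05, no planned sex imbalance, and 3,000 simulated trials per scenario.

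| | *b* = 0.5, without sex | *b* = 0.5, with sex | *b* = 0.7, without sex | *b* = 0.7, with sex |
|---|---|---|---|---|
| Standard error | 1.476 | 1.464 | 1.217 | 1.212 |
| Type I error | 3.4% | 3.7% | 3.7% | 3.8% |
| Power at 0.20 SD | 50.1% | 50.4% | 65.9% | 66.3% |

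The standard error falls by less than 1%, and type I error is not inflated without sex.

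**The case against.** The strongest case for leaving this alone has five parts.

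- **Silence is not exclusion.** A reader might infer that the plan adjusts for baseline and nothing else. The text does not say so, several models are announced, and a journal article commonly leaves its covariate list to the full analysis plan. This stands: there is no omission to criticise, only a covariate worth naming.
- **The trial compares arms, not sexes.** A reader might infer that the model is wrong because boys and girls with equal baseline are predicted alike. The hypothesis concerns the arm contrast, and a prognostic factor left out of both arms alike does not bias it. This stands; the harm requires an imbalance in sex.
- **The entry rule is not the cause.** It is tempting to blame the sex-specific cut-offs of 61 and 54. The gap formula contains no cut-off, and selection on baseline leaves the regression of outcome on baseline unchanged. The cause is the difference in means. The cut-offs matter only because they show that the plan regards sex as prognostic and has it on record.
- **The inputs are uncertain.** The norms describe children in general, whereas these children come forward because they or their parents see them as sadder or more anxious than their peers. The gap among them may not be seven points. The article also gives no reason to expect the share of girls to differ by arm; knowledge of allocation makes that possible, no more. Both limits stand and are carried as assumptions. If recruitment does differ by arm, differences in motivation or severity could matter more, and a sex covariate would not remove them.
- **SMFQ.** It has a single norm for both sexes, so the argument gives no ground for changing the SMFQ models.

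What remains is narrow: by the plan's own figures sex predicts MASC, chance or selective recruitment can unbalance it, and adjusting for it costs almost nothing.

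**Conclusion.** The point holds as a minor improvement to the MASC analysis. If the seven-point gap carries over and the slope lies between 0.4 and 0.8, a 10-point imbalance in the share of girls moves the MASC effect by roughly 0.01 to 0.03 SD against a planned 0.35 SD, and even 20 points moves it by at most about 0.06 SD. Precision gains are small. An imbalance of this size is unlikely to change the trial's conclusion unless the result is borderline. The documents do not support calling the planned comparison invalid or the analysis wrong.

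**What to change.** In the Planned statistical analysis section, or in the full analysis plan if that is where covariates are listed, name sex as a prespecified fixed covariate alongside baseline score in the MASC outcome models. If it is already listed there, nothing more is needed. The SMFQ models can stay as they are. The cost is one degree of freedom and a few words; sex must already be known to apply the MASC norm, so no new data are required. The covariate should be fixed before outcome data are examined by arm, so that its inclusion cannot depend on the result.

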**Table 1 Tab1:**
[figure not shown]
SPIRIT table for evaluation of the EMOTION Coping Kids RCT

^a^Enrollment occurs in the semester prior to delivery of the intervention. Each cohort represents a group of children recruited during the semester

^b^Allocation (randomization) is conducted at the school-level, therefore allocation reflects when new schools joined the study

^c^Study eligibility for individual children is based on their scores on the MASC and SMFQ (primary outcome measures)

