### Blinding

Because of the nature of the current interventions, it is not possible for the participants to be unaware of the intervention condition they are assigned to after baseline. Furthermore, schools are randomized to either EMOTION or TAU prior to participation (see Randomization), so most participants are aware of the treatment condition prior to the baseline assessment.

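### Low-severity free improvement: entry depends on both SMFQ and MASC, so each primary model could state adjustment for both baselines rather than just for baseline level

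*Protocol article*

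**What the plan says.** Under Inclusion criteria, the children invited are those "who score at least one standard deviation above the expected mean score for either depression" or anxiety, or both. The footnote to Table 1 confirms the overlap with the outcomes: "Study eligibility for individual children is based on their scores on the MASC and SMFQ (primary outcome measures"). Under Primary outcomes, the targets are named as follows: "The primary outcomes of interest for this study are the changes in depression and anxiety from pre- to post-intervention and from pre-intervention to follow-up".

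On timing, the Randomization section says that "study participants may know prior to offering their consent for participation whether they would receive EMOTION or be in a control school", and the Blinding section says that "most participants are aware of the treatment condition prior to the baseline assessment".

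The only adjustment stated for the arm comparison is in Planned statistical analysis: regression models that respect the hierarchical structure, "to compare the active intervention versus controls adjusting for baseline level". The sentence does not list the baseline variables, and it does not exclude any.

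**The concern.** Two variables decide entry. On the natural reading, each primary model conditions on one of them. In an individually randomised trial with concealed allocation, the second score would matter for precision and little else. Here schools are randomised first, families volunteer in response to an open letter, and most children answer the entry questionnaires knowing their arm. Randomisation therefore does not guarantee that both arms recruit the same mix of children who qualify on anxiety and children who qualify on depression.

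One might expect the outcome's own baseline to stand in for the other score, since the two scales are presumably correlated. Selection undoes this. A child below the SMFQ cut-off is in the trial only because MASC is high, while a child above it may have any MASC score. If the entry mix differed by arm, part of that difference would be carried into the estimated effect of EMOTION against TAU on each primary outcome. Some precision would also be given up.

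**Working it through.** **The plan's own figure.** For a standardised effect of 0.35, two-sided 0.05 and power 0.80, the unclustered requirement is 129 per arm, 258 in total (the article uses 260). The design effect is 1 + (24 − 1) × 0.05 = 2.15, and 260 × 2.15 = 559. Power at 559 / 2.15 = 260 effective children is 0.806. The figure reproduces. It takes no credit for covariates, so nothing below makes it wrong.

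**Inputs from the article.** The cut-offs are 3.8 + 3.6 = 7.4 on SMFQ, and 46 + 15 = 61 (girls) or 39 + 15 = 54 (boys) on MASC, either or both. The planned effect is 0.35.

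**Assumed inputs (the article gives none).** Scores are bivariate normal in norm-SD units, and the entry scores serve as the baselines. The same-time correlation between the scales is r = 0.3 to 0.5, the own-scale correlation over time is s = 0.4 to 0.5, and the cross-scale correlation over time is c = 0.30 to 0.40. The arm gap in the other score, at equal own baseline, is 0.2 SD (0.2 × 3.6 = 0.72 SMFQ points or 0.2 × 15 = 3 MASC points). The effect of 0.35 is treated as being on the same SD scale.

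**Step 1: what the entry rule does to the correlation.** Simulate pairs and keep those with either score at least 1 SD above the norm.

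| Assumed correlation before selection | Correlation among entrants | Same, if volunteers average 0.5 SD above the norm |
|---|---|---|
| 0.3 | about −0.38 | −0.23 |
| 0.5 | about −0.21 | −0.05 |
| 0.7 | about +0.06 | +0.23 |

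The own baseline says little about the other score, or points the opposite way.

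**Step 2: slope on the other score.** With both baselines in a linear model, the slope on the other score is b = (c − r·s) / (1 − r²). The bias from leaving that score out is b × gap, and the cut in residual variance is read from the simulated entrants.

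| r | s | c | b | Bias at 0.2 SD gap | Share of 0.35 | Variance cut |
|---|---|---|---|---|---|---|
| 0.3 | 0.4 | 0.40 | (0.40 − 0.12)/0.91 = 0.308 | 0.062 | 18% | 8.6% |
| 0.3 | 0.5 | 0.40 | (0.40 − 0.15)/0.91 = 0.275 | 0.055 | 16% | 7.7% |
| 0.5 | 0.5 | 0.40 | (0.40 − 0.25)/0.75 = 0.200 | 0.040 | 11% | 3.4% |
| 0.5 | 0.5 | 0.30 | (0.30 − 0.25)/0.75 = 0.067 | 0.013 | 4% | 0.4% |

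The first and last rows are the extremes of the assumed grid. In scale points the bias runs from 0.013 × 3.6 = 0.05 to 0.062 × 3.6 = 0.22 on SMFQ, and from 0.013 × 15 = 0.2 to 0.062 × 15 = 0.9 on MASC.

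**Step 3: sensitivity.** When c = r·s, b is zero, and so are the bias and the precision gain; for example r = 0.3, s = 0.5, c = 0.15. At r = 0.3, s = 0.5, c = 0.20 the bias is 0.011 SD (3%) and the variance cut 0.3%. At r = 0.7, s = 0.5, c = 0.30 the sign reverses: b = (0.30 − 0.35)/0.51 = −0.098 and the bias is −0.020 SD.

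**Step 4: precision in terms of power.** A variance cut of 1%, 4% or 9% is equivalent to needing 553, 537 or 509 children instead of 559. At 559 children, power rises from 0.806 to 0.809, 0.821 or 0.841.

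**Step 5: gaps that arise by chance.** With 559 children, the standard error of an arm gap in the other score is √(4/559) = 0.085 SD without clustering. With an ICC of 0.05 it is 0.124 SD at 24 children per school (√(4 × 2.15/559)), or 0.111 SD at 559/36 = 15.5 per school. A gap of this kind is noise that the standard error of the treatment effect already covers.

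**The case against.** The strongest reply is that the analysis sentence contains nothing incorrect. It is one general statement covering several models in a journal article, and covariate lists usually sit in the full protocol or analysis plan, which is not shown. A reader might infer that the models adjust for the outcome's own baseline and nothing else. The article does not say so, and that restriction is only the natural reading of an undefined term. Adjusting each outcome for its own baseline is also standard practice. All of this stands, and it is why the point is an improvement and not a defect.

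A reader might also infer that arm differences in the other score will in fact bias the result. The documents do not support that. The same entry rule applies in both arms, and nothing indicates that EMOTION or TAU schools would attract more children through anxiety than through depression. The 0.2 SD gap is an assumption. If recruitment does not depend on arm, the gap is zero in expectation. The bent relation at the cut-off and the flattened own-baseline slope arise from a rule common to both arms, so they do not by themselves bias the comparison.

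The sizes also lean on chosen correlations. The largest figures need a cross-scale correlation over time (0.40) above the same-time correlation (0.3), which is an unlikely ordering.

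What remains is that awareness of allocation before baseline makes a difference in entry mix possible, that own-baseline adjustment would not remove it, and that the remedy costs almost nothing.

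**Conclusion.** The point holds as a low-severity, no-cost improvement. Entry rests on two scores, the stated adjustment most naturally uses one, and the either/or rule prevents that one from standing in for the other. Within the assumed ranges and with a 0.2 SD arm gap, the bias left is about 0.01 to 0.06 SD (4 to 18% of 0.35), and the second score cuts residual variance by about 0.4 to 9%. Both rest on correlations that the article does not report and can be near zero under other plausible values. The bias also requires that the entry mix really differs by arm. No figure in the article is wrong, and the article does not contradict itself on this point.

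**What to change.** In Planned statistical analysis, replace the undefined reference to baseline level with: *Each primary model (SMFQ and MASC) adjusts for both the baseline SMFQ score and the baseline MASC score.* Leave the rest of the model as it is.

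The cost is one more covariate per primary model. Both scores are already held for every entered child because they decide entry, so there is no added data collection or burden. The sentence also settles which baselines are meant before outcome data are seen. It has a limit: it removes only the part of any recruitment difference that these two self-reported scores measure, and mostly arm-aware children supply those scores. It does not cure the wider problem of recruiting after allocation is known.
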